# Efficacy and safety of Yi Shen Fang granules in elderly people with MCI: study protocol for a multicentre, randomized, double-blind, parallel-group, controlled trial

**DOI:** 10.1186/s12906-023-03940-x

**Published:** 2023-04-03

**Keywords:** Traditional Chinese medicine, Cognitive, Mild cognitive impairment, Clinical trial

## Abstract

**Background:**

Mild cognitive impairment (MCI) is a transitional state between normal ageing and dementia. Most MCI patients will progress to dementia within 5 years; therefore, early intervention for MCI is important for delaying the occurrence and progression of dementia. Yi Shen Fang (YSF) granules are a promising traditional Chinese medicine (TCM) treatment that shows great neuroprotective potential against cognitive impairment, as evidenced in clinical and basic studies. This trial aims to systematically evaluate the efficacy and safety of YSF granules in elderly people with MCI.

**Methods:**

This study is a multicentre, randomized, double-blind, parallel-group, controlled trial. Based on the results of previous clinical trials, 280 elderly patients with MCI will be randomly divided into a treatment group (*n* = 140) and control group (*n* = 140). The study will last 33 weeks, including 1 week of screening, 8 weeks of intervention, and 24 weeks of follow-up. The primary outcomes will be the changes in Montreal Cognitive Assessment (MoCA) and Memory and Executive Screening (MES) scores before and after the intervention. The secondary outcome measures will be homocysteine (HCY) levels, Functional Assessment Questionnaire (FAQ) scores and event-related potential (ERP) detection in typical cases. The TCM symptom scale is a combined measure of syndrome differentiation and treatment. During this study, the classifications and characteristics of adverse events, the times of occurrence and disappearance, the measures of treatment, their impact on the primary disease, and outcomes will be reported truthfully.

**Discussion:**

This study will provide valuable clinical evidence that YSF can help to improve the cognitive function of elderly people with MCI, and the results will be disseminated via conferences and publications.

**Trial registration:**

Chinese Clinical Trial Registry, ChiCTR2000036807. Registered on August 25, 2020.

**Supplementary Information:**

The online version contains supplementary material available at 10.1186/s12906-023-03940-x.

## Background

Chinese people aged 60 and older numbered 264.02 million, or 18.7% of the total population, according to the National Bureau of Statistics of China in the 2020 census. As the Chinese population ages and ageing-associated diseases increase at a rapid rate, the prevalence of dementia among individuals aged 60 years and older was found to be 6.0%, and mild cognitive impairment (MCI) was estimated in 15.5% of individuals of this age group in China [1]. MCI refers to a cognitive decline that does not impair cognitive function significantly, which is generally referred to as a transition state between normal cognition and Alzheimer's disease [2], and compared with normal cognition, MCI is more likely to develop into Alzheimer's disease [3]. Undoubtedly, cognitive impairment is an extremely serious problem, and effective therapy should be administered before the disease worsens. Cholinesterase inhibitors (ChEIs) are commonly used for treating MCI, with very little evidence showing that they can prevent the progression from MCI to dementia. The efficacy of ChEI treatment for MCI remains controversial [4–6]. Thus, novel strategies and prevention methods need to be explored for MCI treatment. We hope that TCM can produce positive effects on clinical treatment, increasing patients’ confidence in the use of Chinese herbs, which can further enhance the efficiency of prevention and treatment.

In recent years, an increasing number of studies have shown that traditional Chinese medicine has a potential multitarget therapeutic effect on early MCI and exerts neuroprotective effects, showing certain application prospects [7–11]. Yi Shen Fang (YSF) granules are traditional Chinese herbal compounds that have been commonly used in MCI treatment in our specialist outpatient clinic. A previous clinical study indicated that YSF could improve cognitive function in elderly patients, especially by improving naming, attention, and delayed recall ability. YSF granules consist of Xiangfu (*Cyperus rotundus*), Rougui (*Cinnamomum verum*), Sharen (*Amomum dealbatum*), Shanzhi (*Gardenia jasminoides*), Shichangpu (*Acorus calamus*), Yuanzhi (*Polygala tenuifolia*), and Xuancaohua (*Hemerocallis lilioasphodelus*).

In previous research on YSF in the treatment of cognitive impairment in vascular dementia rats carried out by our research group, we established rats with two-vessel occlusion and middle cerebral artery occlusion as a vascular cognitive impairment (VCI) rat model [12]. The results of the experiment showed that YSF could inhibit the apoptosis of hippocampal neurons and improve the spatial search ability and localization of VCI rats by regulating the BDNF-TrkB pathway and expression of mTOR protein in the hippocampus [13], which was sponsored by the Natural Science Foundation of Shanghai (No. 17ZR1428100). Based on the above basic research results, we performed a multicentre, double-blind, randomized controlled study of YSF granules combined with acupuncture for elderly adults with MCI to further verify the clinical efficacy on cognitive function. The preliminary results showed that YSF granules combined with acupuncture could improve cognitive function, especially the visuospatial and executive ability of elderly patients with MCI (unpublished data). YSF has been granted the patent of invention by the China National Intellectual Property Administration (Patent No. 201810784587.8) as a TCM composition to improve VCI. Therefore, the aim of this trial is to objectively evaluate the clinical efficacy and safety of YSF in the treatment of elderly patients with MCI based on our previous studies and to further provide a new therapy and clinical basis for the treatment of MCI with TCM.

## Methods

### Study design

This study is a multicentre, randomized, double-blind, parallel-group, controlled trial. The objective of this trial is to evaluate the clinical efficacy and safety of YSF granules in elderly patients with MCI. The trial protocol (version 2.0, April 27, 2020) has been registered with the Chinese clinical trial registry (No. ChiCTR2000036807). The period for research recruitment is from August 5, 2021, to December 31, 2023. We present the following article in accordance with the SPIRIT 2013 reporting checklist. For more details about the checklist, please see Additional file 1.

Before the beginning of the clinical study, all researchers will be trained on the standardized process and scale evaluation consistency to ensure the clinical trial quality and data credibility of each centre. A total of 280 elderly patients with MCI will be randomly divided into a treatment group and a control group in a 1:1 allocation ratio. It will be carried out in three clinical centres in Shanghai, 140 subjects will be recruited at Shanghai Municipal Hospital of TCM, and we plan to recruit 70 subjects from Shanghai Qingpu District Hospital of TCM and 70 subjects from Shanghai Jiading District Nanxiang Hospital. All participants will experience a 1-week screening period, with an 8-week treatment period and follow-up visits at 24 and 48 weeks. The primary efficacy outcome measures will be the change in the Montreal Cognitive Assessment (MoCA) and Memory and Executive Screening (MES) scores, which will be used to assess cognitive function following the interventions. The TCM symptom scale is a combined measure of syndrome differentiation and treatment. Safety outcome markers will include hepatic and renal functions, electrocardiogram data, routine blood and urine test results, and severe clinical discomfort. The schedule of enrolment, interventions, assessments and data collection is presented in Table 1. The study will follow the Helsinki Declaration and the Good Clinical Practice guidelines. Ethical approval was granted by the Ethics Committee of Shanghai Municipal Hospital of TCM (approval no. 2020SHL-KY-06). Each subject could only be included in this study once and signed an informed consent form prior to study participation. The results of the study will help provide a clinical basis and TCM treatment plan for standardized diagnosis and treatment of MCI. The flowchart of this study is illustrated in Fig. 1.

**Table 1 Tab1:** Schedule of enrolment, interventions, and assessments

	STUDY PERIOD					
**STUDY PROCEDURE**	Enrolment	Allocation	Post-allocation		Follow-up	
**TIMEPOINT**	-1-week	0-week	4-week	8-week	12-week	24-week

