#### Primary outcomes

Cognitive status will be evaluated with the MoCA and MES. The primary efficacy endpoints are the improvement rate for MoCA scores and MES scores, which will be measured before and after treatment in both groups. The MoCA has high sensitivity and specificity in distinguishing normal elderly individuals from those with MCI and mild Alzheimer's disease and can detect slight cognitive impairment [16]. The MES has been confirmed to be a valid and easily administered screening tool for MCI, and the score is independent of education and can also be used to evaluate individuals [17].

$$\text{Improvement rate} = \left[\left(\text{posttreatment score}-\text{pretreatment score}\right)/\text{pretreatment score}\right]\times100\%.$$

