#### Safety evaluation

For the safety evaluation, routine blood, liver function (alanine aminotransferase (ALT) and aspartate aminotransferase (AST)), renal function (blood urea nitrogen (BUN) and creatinine (Cr)), urine, and faecal tests and electrocardiograms will be performed before treatment and after 8 weeks of intervention. Vital signs and all adverse events will be recorded at every study visit during the trial. In case of any adverse event during the study, the clinician in charge of the case shall carefully record the details, including the name and characteristics of the adverse event, occurrence and disappearance time, treatment measures, impact on the primary disease and prognosis, in the CRF.

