### Statistical analyses

In this study, the data analysis will be performed on the full analysis set (FAS), per protocol set (PPS) and safety analysis set (SS). The efficacy analysis will be conducted on an intention-to-treat (ITT) basis. The 95% confidence intervals (CIs) will be calculated as exact CIs. For the two primary outcomes, the *P*-value will be adjusted to 0.033. This value was based on a recommendation to divide the pre-specified *P*-value threshold by the value halfway between 1 (representing no adjustment) and the number of primary outcome comparisons (the denominator used for the Bonferroni correction) [23]. All statistical tests are 2-sided, and unless otherwise stated, *P* < 0.05 will be considered statistically significant. When the primary outcome measures are missing, the researchers will combine statistical analysis and clinical experience to judge whether to exclude the subject or replace the missing data with the last observation carried forward (LOCF).

The measurement data will be subject to normal distribution and homogeneity of variance, which is expressed as the mean ± standard deviation. Comparisons between groups will be performed using an independent 2-sample t test. Comparisons between multiple time points will be analysed using repeated-measures ANOVA, multivariate ANOVA or paired t test. When the data do not meet the criteria of normality and homogeneity, the results will be expressed as the median. The Wilcoxon rank sum test will be used to compare differences between groups. Before and after treatment, numerical variables and ordered categorical variables measured over multiple time points will be analysed using generalized estimating equations and a mixed effects model. The enumeration data will be expressed as frequency (n), constituent ratio (%) or ratio (%). If the variable data type is unordered, categorical comparisons between groups will be performed by the χ^2^ test. The ordered categorical variable data will be analysed using the rank sum test. Comparisons of two-way ordered data with different properties within contingency tables will be made with the linear chi-square test or rank sum test. Multivariate data analysis will be conducted using multiple linear regression, the K-M test, Cox regression or a trend test. All statistical analyses will be performed with IBM SPSS Statistics 24.0.

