### Limitations

The following issues are considered limitations of the study. First, the 8-week treatment cycle in this study is relatively short. Cognitive impairment may require long-term maintenance medication to delay the development of the disease to prevent progression to dementia. Second, biomarkers and neuroimaging characteristics associated with MCI in the early symptomatic period are not yet clear. The changes in ERP and serum HCY may not fully reflect the curative effect of TCM on MCI. Subjective measurements combined with imaging may need to be performed to find the correlation between early brain tissue changes and MCI in further studies. Third, participants in this trial have fewer comorbidities. MCI is often comorbid with cardiovascular and cerebrovascular diseases, neurodegenerative or affective disturbance [33, 34], but the trial is aimed at increasing the pertinence of inclusion criteria and standardizing the drug to the disease, so it lacks certain generalizability. Finally, the 6-month follow-up period is rather short. MCI is a chronic, progressive disease that requires long-term follow-up to assess cognitive changes. Therefore, we may not observe the key node of cognitive impairment, further development, or transformation after the termination of treatment.

Bearing these limitations in mind, we will conduct long-term follow-up to record the prognosis of MCI patients treated with Chinese herbs. There is a dire need to strengthen health care systems with additional medical institutions and place more emphasis on the health of elderly people to improve the quality of life of these individuals. We are calling for more effective ways of delaying the progress of cognitive impairment as well as improve the prognosis.

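### Study design puts the follow-up visits at 24 and 48 weeks, which contradicts Table 1 (12 and 24 weeks) and the 33-week total; Table 1 also leaves the origin of its follow-up weeks unstated

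*Protocol article*

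**What the plan says.** The protocol article gives the follow-up timing in four places.

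- **Methods, Study design:** the 1-week screening period is followed by treatment and follow-up, "with an 8-week treatment period and follow-up visits at 24 and 48 weeks". Later in the same section: "The schedule of enrolment, interventions, assessments and data collection is presented in Table 1".
- **Table 1:** a single timepoint row runs −1, 0, 4, 8, 12 and 24 weeks. Week 0 stands under allocation, and weeks 12 and 24 stand under follow-up. There is no 48-week column, and no heading or footnote says what the follow-up weeks are counted from.
- **Abstract, Methods:** "The study will last 33 weeks, including 1 week of screening, 8 weeks of intervention, and 24 weeks of follow-up".
- **Discussion, Limitations:** "the 6-month follow-up period is rather short". The paragraph goes on to what may go unobserved once treatment has ended.

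Three other sections determine what the conflict touches. Table 1 schedules MoCA, MES, FAQ, the TCM symptom scale and adverse events at both follow-up visits. Safety evaluation adds: "Vital signs and all adverse events will be recorded at every study visit during the trial". Statistical analyses states: "Comparisons between multiple time points will be analysed using repeated-measures ANOVA, multivariate ANOVA or paired t test". The primary endpoints are the MoCA and MES improvement rates, "which will be measured before and after treatment in both groups".

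**The concern.** The Study design text names a 48-week visit that appears in no other visible part of the article, omits the 12-week visit, and contradicts the table it cites. Table 1 cannot simply be taken as the answer either, because its natural reading (weeks from allocation) does not add up to the duration in the abstract.

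What is at stake is the post-treatment part of the trial: how long after the last dose the cognitive, functional and symptom scores are taken, and how long adverse events are collected off treatment. The article describes MCI as chronic and progressive, so an effect that lasts 16 weeks off treatment is a different claim from one that lasts 48. A site that worked from the Study design sentence would see patients at different times from a site that worked from Table 1. Nothing in the article shows that this has happened; it is a risk to check.

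**Working it through.** **Inputs**

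- Screening, 1 week: abstract and Study design.
- Treatment, 8 weeks: abstract, Study design and Interventions.
- Follow-up, 24 weeks, and total, 33 weeks: abstract.
- Follow-up visits at 12 and 24 weeks: Table 1.
- Follow-up visits at 24 and 48 weeks: Study design.

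**The plan's own figure.** Total = screening + treatment + follow-up = 1 + 8 + 24 = 33 weeks. The abstract is internally consistent.

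**Each visit schedule under each origin.** If weeks count from allocation, total = 1 + last visit, and time since treatment = visit − 8. If weeks count from the end of treatment, total = 1 + 8 + last visit, and study week = 8 + visit.

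| Source and origin | Study weeks of visits | Last visit, weeks after treatment | Total duration | Against 33 weeks |
|---|---|---|---|---|
| Table 1, from allocation | 12, 24 | 24 − 8 = 16 | 1 + 24 = 25 | 8 short |
| Table 1, from end of treatment | 20, 32 | 24 | 1 + 8 + 24 = 33 | agrees |
| Study design, from allocation | 24, 48 | 48 − 8 = 40 | 1 + 48 = 49 | 16 over |
| Study design, from end of treatment | 32, 56 | 48 | 1 + 8 + 48 = 57 | 24 over |

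Neither Study design row matches the abstract. Of the two Table 1 rows, only the one counted from the end of treatment does. Depending on which statement is followed, the final visit falls at week 24, 32, 48 or 56 from allocation.

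**Against the 6 months in Limitations.** At 4.345 weeks per month, post-treatment follow-up is 24 / 4.345 ≈ 5.5 months for Table 1 counted from the end of treatment, and 16 / 4.345 ≈ 3.7 months for Table 1 counted from allocation. For Study design it is 40 / 4.345 ≈ 9.2 months or 48 / 4.345 ≈ 11.0 months. The first is the closest to 6.

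**What is affected per patient.** Four scales (MoCA, MES, FAQ, TCM symptom scale) are each scheduled at six time points, 4 × 6 = 24 assessments. Two of the six time points are follow-up visits, so 4 × 2 = 8 of 24 have uncertain timing. Adverse events are scheduled at four time points, two of them in follow-up.

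**What is not affected.** The primary endpoints use scores before and after treatment. The MoCA sample size of 104 per group before allowances does not involve follow-up time. ERP and HCY are measured at weeks 0 and 8, and the laboratory safety tests at screening and week 8.

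**The case against.** The strongest reply is that this is one wrong sentence. The abstract spells out its components, Table 1 has no week 48, and a careful reader would discard the Study design figure; what then remains open is only whether the last visit is 16 or 24 weeks after treatment. That narrows the practical doubt fairly. But the sentence stands in the Methods, and correcting it to 12 and 24 weeks would still leave the 8-week gap between the two readings of Table 1.

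A second reply is that Table 1 has one continuous axis with week 0 at allocation, so its origin is clear enough. That is the natural reading, but it gives 25 weeks against the stated 33, so either the table or the abstract needs correcting. The text alone does not prove which, and the fix has to depend on the sponsor's answer.

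Third, 6 months is a loose figure and could be counted from allocation. This has some force, although Limitations speaks of what happens after treatment stops. The decisive conflict is with the abstract's explicit sum.

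Other caveats:

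- Fig. 1 and the full protocol (version 2.0) are not shown. Either may state the schedule correctly, but neither can make the published statements agree.
- The planned comparisons over multiple time points do not name the follow-up visits, so their dependence on them is an inference.
- The count of 24 covers only the four repeated scales. Adding the screening-only HAMA, GDS and CDR gives 27, and the affected number stays at 8.

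**Conclusion.** The concern holds. The 24- and 48-week visits in Study design fit neither Table 1 nor the abstract under any origin, and overshoot the stated duration by 16 or 24 weeks. Separately, the unlabelled follow-up columns of Table 1 leave an 8-week uncertainty about the last visit: 16 or 24 weeks after treatment.

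The most coherent reading is 12 and 24 weeks after the end of treatment. It rests on taking the abstract's 33 weeks as correct, which the sponsor has to confirm. The error should be fixed because it governs when outcomes and adverse events are collected, but its reach is limited to post-treatment follow-up. The primary analysis and the sample size stand as they are.

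**What to change.** 1. Have the sponsor confirm the intended origin of the follow-up weeks.
2. In Study design, replace the 24- and 48-week visits with the Table 1 follow-up visits, stating the origin.
3. Add a footnote to Table 1 giving the origin. If the 33-week total is right, the columns are 12 and 24 weeks after the end of treatment, study weeks 20 and 32. If the weeks run from allocation, keep study weeks 12 and 24, change the abstract to 16 weeks of follow-up and 25 weeks in total, and revise the 6 months in Limitations.
4. Ask the three sites which schedule they have used since recruitment began in August 2021. Only if they differed, analyse the follow-up scores by actual time since allocation.

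The cost is one corrected sentence, one footnote and one query to three sites, plus two small text changes if the allocation-based reading is the intended one. No new procedures are needed. Trial status reports recruitment still in progress, so the clarification can still serve visits to come.

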**ENROLMENT**						
Eligibility screen	×					
Informed consent	×					
Allocation		×				
**INTERVENTIONS**						
Intervention group			×	×		
Control group			×	×		
**ASSESSMENTS**^**a**^						
HAMA	×					
GDS	×					
CDR	×					
MoCA	×	×	×	×	×	×
MES	×	×	×	×	×	×
FAQ	×	×	×	×	×	×
TCM symptom scale	×	×	×	×	×	×
ERP		×		×		
HCY		×		×		
**SAFETY ASSESSMENTS**						
Laboratory tests^b^	×			×		
**Adverse events**			×	×	×	×

^a^Assessments: *HAMA* Hamilton Anxiety Scale, *GDS* Geriatric Depression Scale, *CDR* Clinical Dementia Rating Scale, *MoCA* Montreal Cognitive Assessment Score, *MES* Memory and Executive Screening, *FAQ* Functional Assessment Questionnaire, *TCM Symptom Scale* Traditional Chinese Medicine Symptom Scale, *ERP* event-related-potentials, *HCY* homocysteine

^b^Laboratory tests: routine blood, hepatic (*ALT* alanine aminotransferase, *AST* aspartate aminotransferase) and renal (*BUN* blood urea nitrogen, *Cr* creatinine) functions, urine, faecal and electrocardiogram

**Fig. 1 Fig1:**
[figure not shown]
Flowchart of the study trial. YSF: Yi Shen Fang; HAMA: Hamilton Anxiety Scale; GDS: Geriatric Depression Scale; CDR: Clinical Dementia Rating Scale; MoCA: Montreal Cognitive Assessment Score; MES: Memory and Executive Screening; FAQ: Functional Assessment Questionnaire; TCM Symptom Scale: Traditional Chinese Medicine Symptom Scale; ERP: event-related-potentials; HCY: homocysteine

